### Image analysis

Ultrasound images will be extracted from the ultrasound machine and analyzed offline. Using publicly available software (ImageJ, National Institutes of Health), the fascicle length, pennation angle, and muscle thickness from the extended-field-of-view and static B-mode longitudinal images will be analyzed according to previous methods [68, 69]. Anatomical cross-sectional area will be calculated from transverse images at the proximal, mid-belly, and distal locations.

### Outcome measures & statistical analysis

All outcome results will be included in an anonymous database for statistical analysis. Using an intention-to-treat analysis, separate linear mixed effects models will be used to compare the effect of RDL and NHE on the primary outcome of biceps femoris long head fascicle length. Similar analyses will be performed for secondary analyses related to pennation angle, anatomical cross-sectional area, muscle thickness, and SWS. Full factorial models will be implemented with fixed effects of intervention group, muscle region, and time and a random effect to account for between-participant variation. Effect sizes will be calculated.

Sprint performance outcomes will be summarized using descriptive statistics. Given that the expected changes in sprint performance are numerically small but may still represent meaningful changes in overall sport performance and improvement, we will set *a priori* thresholds to describe the magnitude of change. Small, medium and large improvements in sprint times will be defined as < 2%, 2–4%, and > 4%, respectively, based off changes in 40 m sprint times observed previously [47, 82].

Discrete kinematic variables will be summarized using descriptive statistics and compared between time points for the maximal sprint using linear mixed effects models [83]. Due to the continuous time series data extracted from the IMUs, statistical parametric mapping (SPM) will also be used to determine any within-participant changes in kinematics throughout the entire sprint. SPM allows for the analysis of the entire time series and has been used in a variety of biomechanical studies [84–86]. Specifically, within-subject differences in trunk, hip, knee, and ankle kinematics will be calculated between test sessions

As an additional description of sprint performance, we will characterize the horizontal force production as detailed by Samozino et al. and adapted by others [1, 47, 87]. Descriptions of the theoretical maximal horizontal force (F_0_), velocity (v_0_), and maximal power output (P_max_) will be derived from participants’ split times and each participant’s body mass according to previous works [44, 88]. Intervention assessments for each variable across each time point will be compared using linear mixed effects models and R software [89, 90]

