## Methods/Design

### Overall study design

This study is a randomized intervention trial where participants will be allocated to one of two experimental groups: RDL or NHE training. The primary outcome of the study is the change in regional biceps femoris fascicle length between the two intervention groups. Secondary outcomes will include ultrasound-derived changes in pennation angle, muscle thickness, anatomical cross-sectional area, in addition to hamstrings strength, and maximal sprint performance. As an exploratory aim, we will determine changes in regional SWS following training and between the two intervention groups.

The study is registered on ClinicalTrials.gov (Identifier: NCT05455346) with all procedures approved by the Health Sciences Institutional Review Board at the University of Wisconsin-Madison. Written informed consent will be obtained from all participants before inclusion by study personnel with Human Subjects Protection training. Any changes in the protocol will be reflected on the clinical registration website of ClinicalTrials.gov.

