An overview of the experimental design is given in Fig. 1. Inclusion criteria for participants eligible for the intervention trial are 18–25 years of age (consistent with previous investigations [29, 47, 54]), self-report of being physically active—as defined by the Physical Activity Guidelines for Americans [55],, having > 6 months experience in resistance training, no history of HSI within the last 6 months, no history of lower extremity surgery, no current musculoskeletal injury to the lower extremity, and females not currently pregnant. Physical activity will be defined as participating in weekly totals of 150–300 min (5 h) of moderate-intensity, or 75–150 min (2 h and 30 min) of vigorous-intensity aerobic physical activity, or an equivalent combination of moderate- and vigorous-intensity aerobic activity. Prior to the intervention, baseline assessments will be performed. These include regional ultrasound measures (see *Ultrasound Measures*); strength for the NHE and RDL (see *Nordic Hamstring Exercise and Romanian Deadlift Strength Testing*); and maximal 60 m sprints (see *Maximum Sprint Testing*). Each participant will also be asked to complete the Baecke questionnaire for determination of habitual physical activities and what current physical activities pertinent to the study in which they participate at baseline [56]. Participants will be able to continue usual levels and mode of physical activity but be asked to refrain from supplementary lower extremity resistance training and sprint-specific training.

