**Fig. 1 Fig1:**
[figure not shown]
Proposed experimental design and outcome measures at each testing time-point

An *a priori* power calculation using R statistical software and “WebPower” package (wp.kanova function) [57] was performed. Using an effect size based the median Cohen’s d extracted from several relevant studies investigating the effects of NHE on the primary aim of fascicle length changes [19, 21, 26, 54, 58] and converting to Cohen’s f (f = 0.8), 2 experimental groups (RDL vs. NHE), a total of 12 factors (levels of intervention x time x imaging location (proximal, mid-belly, distal) = 2 × 2 × 3), α = 0.05, and power = 0.80, a total sample size of 11 participants per group will be required. This sample size is consistent with previous investigations of fascicle length following NHE training [19, 21, 26, 54, 58]. Using a conservative effect size (Cohen’s d = 0.5) based on observed 2% differences detected in sprint times between two eccentric training interventions (Cohen’s d = 0.87) [47] and converting to Cohen’s f (f = 0.25), a total sample size of 28 (N = 14 per group) will be required for the secondary aims. Based on the larger sample size and accounting for a 10% attrition rate, a total of 16 participants per group (N = 32 in total) will be recruited from the University of Wisconsin to participate. Participants will be compensated on a pro-rated basis for completing study visits and provided their strength and sprint results.

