Participants will be allocated to either the RDL or NHE training group using a random permuted block randomization (1:1 training group allocation) using *a priori* computer-generated group numbers. Each participant will undergo the 6-week intervention program based upon their group allocation (see *Intervention*). A 6-week period was chosen due to previous observations that additional changes in fascicle length (primary outcome) were minimal with NHE training lasting > 6 weeks [47, 59] and is consistent with previous investigations of architectural changes induced by NHE [54, 58]. Following the 6-week intervention, participants will return to the lab for post-intervention assessments of regional ultrasound of the hamstrings, RDL and NHE strength testing, and sprint testing, which will be carried out in the same manner as baseline assessments. Fascicle length changes are known to return to baseline values within 2 weeks after the cessation of NHE [54, 60]. To investigate the potential short-term washout effects of the training intervention on the primary and secondary outcomes, participants will be asked to return to the lab following a 2-week detraining period. During these 2 weeks, participants will be encouraged to resume all normal activities but limit any outside eccentric hamstring strength training.

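### The full-factorial model gives each arm its own baseline mean and so analyses change scores; this is valid, but less precise than an analysis that uses the measured baseline

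*Protocol article*

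**What the plan says.** All places are in the Protocol article.

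- **Outcome measures & statistical analysis:** fascicle length is analysed by linear mixed models. "Full factorial models will be implemented with fixed effects of intervention group, muscle region, and time", plus "a random effect to account for between-participant variation". Pennation angle, anatomical cross-sectional area, muscle thickness and shear wave speed (SWS) get similar analyses.
- **Overall study design, outcome:** "The primary outcome of the study is the change in regional biceps femoris fascicle length between the two intervention groups".
- **Overall study design, visits:** "Prior to the intervention, baseline assessments will be performed". The tests are repeated after week 6 and after two weeks of detraining.
- **Overall study design, power calculation:** the design is counted as "levels of intervention x time x imaging location (proximal, mid-belly, distal) = 2 × 2 × 3". Time is thus a factor, and baseline is one of its levels.
- **Overall study design, allocation:** 1:1 in permuted blocks.

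The article names neither a baseline covariate nor a common baseline mean, and it gives no baseline-to-post correlation.

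**The concern.** A full factorial contains the group main effect and the group-by-region term, so it estimates a separate baseline mean for each arm in each region. Randomisation already makes those means equal in expectation. Estimating them freely discards that information, and the arm comparison becomes a comparison of changes.

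Two things are at stake in a trial of this size. The confidence interval for the primary contrast is wider than the same data allow. And if the arms differ at baseline by chance, a change-score contrast carries part of that difference into the result through regression to the mean.

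**Working it through.** **1. The plan's own figures.**
- Primary: k-way ANOVA F test with f = 0.8, 12 cells, numerator df 2, λ = N × 0.64 and denominator df N − 12. Power is 0.79 at N = 21 and 0.83 at N = 22, so N = 22, the stated 11 per group.
- Secondary: a repeated-measures interaction test with f = 0.25, three time points and correlation 0.5 has λ = 28 × 0.0625 × 3/0.5 = 10.5 on 2 and 52 df, and power 0.81. This matches the stated 28. The three time points and the 0.5 are inferred, not stated.
- Attrition: 28/0.9 = 31.1, which gives 32 in two equal arms.

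The stated sizes reproduce, and nothing below changes them.

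**2. The planned contrast is a change score.** In one simulated data set of this shape (28 participants, three regions, three times, participant intercept), the full-factorial group-by-time coefficient for one region was −0.02244. The arm difference in mean change was also −0.02244. The identity is exact for complete data. With dropout, the mixed model also uses partial records.

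**3. Size for one region.** Take n per arm, common variance σ² and baseline-to-post correlation r (assumed).
- Change score: 4σ²(1 − r)/n
- Baseline-adjusted: 2σ²(1 − r²)/n
- Ratio: (1 + r)/2

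The last two columns take 28 participants in all. Power is for an effect that change scores would detect with 80% power, after a variance inflation of about 1 + 1/24 for estimating the slope.

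| r | ratio | variance saved | N for change scores to match 28 adjusted | power, adjusted |
|---|---|---|---|---|
| 0.5 | 0.75 | 25% | 28/0.75 = 37.3 | 0.89 |
| 0.7 | 0.85 | 15% | 28/0.85 = 32.9 | 0.84 |
| 0.8 | 0.90 | 10% | 28/0.90 = 31.1 | 0.82 |
| 0.9 | 0.95 | 5% | 28/0.95 = 29.5 | 0.80 |

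At r = 0.95 the adjusted power is 0.79, so the slope costs more than it returns.

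**4. Three regions with a common baseline mean.** Let r be the same-region correlation over time and c the correlation between different regions (both assumed), with baseline and one post visit. A working model with a participant intercept only fits one correlation, the average over the 15 pairs: ρ = (3r + 12c)/15 = (r + 4c)/5. It then gives each of the three regional baselines the weight k = ρ/(1 + 2ρ). The true variance of a regional contrast, relative to the planned model, is

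[1 − 2k(r + 2c) + k²(3 + 6c)] / [2(1 − r)].

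Adding a region-within-participant effect gives the matching covariance. The numerator becomes 1 − v′B⁻¹v, with v = (r, c, c) and B the 3 × 3 matrix with 1 on the diagonal and c elsewhere.

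| r | c | k | participant intercept only | with region-within-participant |
|---|---|---|---|---|
| 0.5 | 0.5 | 0.250 | 0.63 | 0.63 |
| 0.5 | 0.3 | 0.202 | 0.75 | 0.71 |
| 0.7 | 0.3 | 0.216 | 1.10 | 0.83 |
| 0.8 | 0.4 | 0.245 | 1.35 | 0.87 |
| 0.8 | 0.3 | 0.222 | 1.54 | 0.88 |
| 0.9 | 0.4 | 0.250 | 2.44 | 0.94 |

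Example (r = 0.9, c = 0.4): ρ = 2.5/5 = 0.5, k = 0.5/2 = 0.25, and (1 − 0.85 + 0.3375)/0.2 = 2.44.

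With the intercept alone, the constraint can more than double the variance. With the extra random effect, the ratio was below 1 in every case tried.

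**5. Chance imbalance.** At 16 per arm the SE of a regional baseline difference is √(2/16) = 0.35 SD, so a gap above 0.5 SD in a given region has probability of about 16%. Given a 0.5 SD gap, the change-score contrast is shifted by (1 − r) × 0.5 SD: 0.25 SD at r = 0.5 and 0.10 SD at r = 0.8.

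**The case against.** The strongest reply is that nothing here is an error. The outcome is defined as a between-group comparison of change, and the model estimates exactly that, without bias under randomisation. This stands, and it limits the point to efficiency.

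A second reply is that r may be high. One blinded operator, standardised skin marks and three longitudinal images per session make good repeatability plausible, and near r = 0.9 little is gained. This also stands. The 0.5 that reproduces N = 28 is an inferred input to a power calculation and says nothing about these measurements.

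A third reply is that the common-baseline model can do harm. It can, if the random part stays a participant intercept. The article itself stresses that architecture and adaptation differ along the muscle, so c below r is plausible. The fix must therefore include the covariance.

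A reader might go further and infer that:
- **the model is invalid or biased:** the shift in step 5 is conditional on a chance imbalance and averages to zero over randomisations;
- **the sample size is wrong or the trial underpowered:** the stated sizes reproduce, and whether f = 0.8 suits a contrast of two active exercises is a separate question;
- **randomisation was unstratified:** the article mentions only permuted blocks, and silence in a condensed article does not settle this.

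**Conclusion.** The point holds as an improvement in efficiency. The stated model fixes a change-score contrast and makes less use of the baseline than it could. For one region the variance saving is (1 − r)/2, and it is worthwhile if r is about 0.8 or lower and small near 0.9. These single-region figures assume equal variances at the two visits and an r that the document does not supply. In the three-region model the saving also depends on the between-region correlation and requires a random part that separates regions within participants. The second benefit is protection against chance baseline imbalance, which is quite possible with 14 to 16 per arm.

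**What to change.** State one of these two analyses for fascicle length:

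1. **Baseline as covariate.** Use the week-6 and post-detraining values as outcomes, with the same region's baseline value as covariate. Keep group, region, time and their interactions.
2. **Common baseline mean.** Keep baseline as an outcome level but drop the group and group-by-region terms at baseline, retaining region, time, region-by-time, group-by-time and group-by-time-by-region. Also add a region-within-participant random effect, or use an unstructured covariance. Option 2 should not be adopted without this second part.

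Apply the same choice to the ultrasound outcomes that share the model: pennation angle, cross-sectional area, muscle thickness and SWS. The sprint outcomes are handled differently in the article (descriptive summaries, comparisons between time points) and are not covered by this point.

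The cost is a few sentences, with no new data, visits or participants. The downside is one estimated slope in option 1 or a somewhat more complex random part in option 2. The choice should be fixed before outcome data by arm are seen.

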**Methods:**

A permuted block randomized (1:1 allocation) intervention trial will be conducted involving young, physically-active men and women. A target sample size of 32 will be recruited and enrolled participants will undergo baseline testing involving extended-field-of-view ultrasound imaging and shear wave elastography of the biceps femoris long head muscle, maximal hamstrings strength testing in both the RDL and NHE, and on-field sprint performance and biomechanics. Participants will complete the 6-week training intervention using either the RDL or NHE, according to group allocation. Baseline testing will be repeated at the end of the 6-week intervention followed by 2 weeks of detraining and a final testing session. The primary outcome will be regional changes in fascicle length with secondary outcomes including pennation angle, muscle cross sectional area, hamstring strength, and maximal sprint performance and biomechanics. An exploratory aim will determine changes in shear wave velocity.

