### Ultrasound

Participants will lay prone on an exam table with their hips and knees in a neutral position and feet off the end of the exam table. Participants will lie quietly at rest for 3 min prior to image acquisition to normalized fluid shift within the muscle [61, 62].

Ultrasound B-mode images will be collected unilaterally from the biceps femoris muscle of the dominant limb for each participant using a Logiq P9 ultrasound system (GE Healthcare, Waukesha, WI) and a linear array transducer (L3-12-RS, 47.1 mm aperture). The same researcher ([name]) will perform all image acquisitions and will be blinded to participant group allocation. The thigh length from the ischial tuberosity to the midpoint between the femoral condyles will be measured and recorded. Skin marks will be made at 33%, 50%, and 67% of the thigh length from the ischial tuberosity to standardize imaging locations between participants and correspond to approximately proximal, mid-belly, and distal regions of the hamstring muscle, respectively [63, 64].

Three longitudinal extended-field-of-view images of the entire biceps femoris muscle (i.e., from the most proximal to the most distal visualization of the muscle-tendon junctions) will be collected. According to extended-field-of-view image acquisition recommendations and previous studies [65–71], preliminary scans will be performed to determine the proximal and distal muscle-tendon junctions A longitudinal image will be captured along the path of the fascicle plane spanning the entire length of the biceps femoris muscle (Fig. 2).

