## Discussion

Although much research has been dedicated to identifying the etiology and mechanisms of injury, potential risk factors, residual neuromuscular deficits, and evidence-based recommendations for rehabilitation protocols of HSI [4, 6, 10, 13, 18, 91–102], the incidence and injury burden of HSI have not improved [14, 103]. The NHE is a staple in injury prevention programs for HSI, but evidence suggests adherence is a major limitation in its effectiveness for reducing HSI [104–107]. Due to the high rate of injury within the proximal muscle-tendon junction of the biceps femoris and non-uniform muscular adaptation to resistance training, different exercises should be employed to target specific muscle regions and increase eccentric training adherence [52, 53, 108, 109]

Consistent eccentric hamstring strength training (specifically using the NHE) increases eccentric knee flexor strength and influences architectural adaptations thought to be protective of HSI—such as increased fascicle length with concurrent decreases in pennation angle [47, 50, 54, 59, 60, 97, 110]. Fascicle length, pennation angle, and muscle thickness are typically measured using ultrasonography at the mid-belly [2, 47, 54, 59, 60], but this does not account for the known variation in architecture along the length of the hamstrings muscles [48, 49, 111, 112] or the non-uniform lengthening, activation, and adaptations induced by resistance training [113–116]. Recent evidence indicated that changes in fascicle and sarcomere lengths only occur in the distal region of the biceps femoris muscle following NHE training [50]. This coincides with higher neuromuscular activation in the distal region compared to the proximal and middle regions of the biceps femoris muscle during the NHE [117]. Our proposed investigation aims to determine if hip-dominant (RDL) or knee-dominant (NHE) eccentric hamstring exercises influence regional differences in fascicle length adaptations

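### The primary model's single participant random effect does not fit 3 regions x 3 visits: the regional interaction test becomes conservative, possibly severely, and the group x time test can err in either direction

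*Protocol article*

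**What the plan says.** In the Protocol article, Outcome measures & statistical analysis, the model for the primary outcome is set out as "Full factorial models will be implemented with fixed effects of intervention group, muscle region, and time", "and a random effect to account for between-participant variation". The same approach is carried over to pennation angle, cross-sectional area, thickness and shear wave speed (SWS). No other random term and no residual covariance structure is named.

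The design gives nine cells per person:
- Three regions (Ultrasound): "Skin marks will be made at 33%, 50%, and 67% of the thigh length from the ischial tuberosity".
- Three visits (abstract, Methods): "Baseline testing will be repeated at the end of the 6-week intervention followed by 2 weeks of detraining and a final testing session". The detraining visit also covers the primary outcome (Overall study design): "To investigate the potential short-term washout effects of the training intervention on the primary and secondary outcomes".

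The target is regional (Overall study design): "The primary outcome of the study is the change in regional biceps femoris fascicle length between the two intervention groups". The Discussion criticises measurement at the mid-belly alone because "this does not account for the known variation in architecture along the length of the hamstrings muscles".

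**The concern.** One participant intercept makes every pair of a person's nine values equally correlated. A proximal value at baseline is taken to be no closer to the same person's proximal value at week 6 than to their distal value at week 6. Two sources of variation are ruled out:
- a person's own regional profile, which persists across visits (participant x region, σ²PR);
- a person's own training response or visit-day shift, shared across regions (participant x visit, σ²PT).

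If either exists, it falls into the residual, and every within-person effect is tested against that one pooled residual. Stable regional anatomy then inflates the error of the regional interaction, although it cancels from any change score. A training response shared by three regions of one person is also counted as three independent replicates when group x time is tested. At stake are the power to answer the regional question and the validity of any claim about the average group difference in change.

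**Working it through.** **The plan's own figures.** The sample size calculation specifies "a total of 12 factors (levels of intervention x time x imaging location" with 2 x 2 x 3 levels. With f = 0.8, noncentrality f²N, 2 numerator df (three-way interaction) and N − 12 denominator df, power is 0.79 at N = 21 and 0.826 at N = 22, so 11 per group reproduces. For f = 0.25, a repeated-measures F test with three measurements and an assumed correlation of 0.5 gives 28; that variant is not stated in the article. Then 28/0.9 = 31.1, rounded up to 32. None of these figures supplies a variance component for fascicle length.

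**Assumptions for the check.** Balanced data, 14 per arm (28 in total), one value per region and visit, residual variance σ²e = 1. All variance ratios are assumed.

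**Error terms.** With 28 − 2 = 26 between-person df, the within-person strata have these expected mean squares:
- participant x region, 2 x 26 = 52 df: σ²e + 3σ²PR
- participant x visit, 52 df: σ²e + 3σ²PT
- participant x region x visit, 4 x 26 = 104 df: σ²e

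In balanced data a single-intercept model pools all 208 df:

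[52(σ²e + 3σ²PR) + 52(σ²e + 3σ²PT) + 104σ²e]/208 = σ²e + 0.75(σ²PR + σ²PT).

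The correct error for group x region x time is σ²e, so the pooled term is too large whenever either component is above zero. The correct error for group x time is σ²e + 3σ²PT. The pooled term is too small when 0.75σ²PR < 2.25σ²PT, that is, when σ²PT > σ²PR/3, and too large when σ²PT is below that.

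**Effect on power.** The effect is set to give 80% power under the correct test, F(4, 104), which needs noncentrality 12.5. The pooled test uses F(4, 208), critical value about 2.41. Worked case (σ²PR 1, σ²PT 0.5): the pooled error is 1 + 0.75 x 1.5 = 2.125, so a noncentral chi-square on 4 df must exceed about 4 x 2.41 x 2.125 = 20.5. The probability of that is about 28%.

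**Effect on group x time type I error.** Worked case (0.5, 1): the correct error is 1 + 3 = 4 and the pooled error is 2.125. Rejection needs F > 3.04 x 2.125/4 = 1.61. For 2 numerator df this has probability of about exp(−1.61) = 0.20.

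**Effect on a region-specific group difference in change.** The participant x region term cancels, so the SE ratio is √[(1 + 0.75(σ²PR + σ²PT))/(1 + σ²PT)]. At (1, 0.5) it is √(2.125/1.5) = 1.19; at (0.5, 1) it is √(2.125/2) = 1.03.

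| σ²PR, σ²PT | Pooled error | Regional interaction power (80% if correct) | Group x time type I error | Region-specific SE too large by |
|---|---|---|---|---|
| 0.25, 0.25 | 1.375 | 62% | about 9% | 5% |
| 0.5, 0.5 | 1.75 | 43% | 12% | 8% |
| 1, 0.5 | 2.125 | 28% | 8% | 19% |
| 0.5, 1 | 2.125 | 28% | 20% | 3% |
| 1, 1 | 2.5 | 17% | 15% | 12% |
| 1, 0 | 1.75 | 43% | under 1% | 32% |

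The table entries come from the exact mean-square distributions, evaluated numerically. With 16 per arm they are nearly the same. For scale, σ²PR = 1 with σ²PT = 0 corresponds, for example, to a same-region test-retest correlation of 0.9 and a between-region correlation of 0.8.

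**The case against.** Three objections carry weight.

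First, every variance component above is assumed. The Discussion's remark about variation along the muscle can refer to mean differences between regions, which the fixed region effect already absorbs. It does not show that people differ in their regional profile. This stands: the size of the error cannot be known from the document. The direction for the regional interaction does not depend on the assumed values, however, and the model is right only if both components are zero. That is hard to expect when the same marked sites are re-imaged in the same people.

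Second, the article is condensed, and one summarising clause need not exclude further terms held elsewhere. It is true that the clause does not expressly limit the model to a random intercept, and missing covariance detail would be no finding. The point is narrower: the structure the article does name, a single random effect at participant level, fits the design poorly.

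Third, a reader might infer that the regional test loses almost all its power and that the trial's p-values are generally too small. The document supports neither. At (1, 0.5), an effect detectable only 44% of the time under the correct test falls to about 5.5%, but the plan aims at 80%, and from there the fall is to 28%. Near-total loss needs larger components: about 6% power remains at σ²PR = 3 with σ²PT = 0. The regional interaction errs only towards missing effects. Inflation is confined to group x time, and large regional variance turns that test conservative. Region-specific contrasts, which also fit the stated primary outcome, can be almost unaffected (3% at (0.5, 1)).

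**Conclusion.** The point holds in a bounded form. As written, the primary model tests all within-person effects against one pooled error that is correct only when participants differ neither in regional profile nor in visit-to-visit response. Otherwise the regional interaction test is conservative. In the five scenarios with both components above zero, its power is 62% down to 17% instead of 80%. The group x time error has no fixed sign: about 8% to 20% in those scenarios, and under 1% at (1, 0). Region-specific standard errors are 3% to 19% too large in the five scenarios and 32% too large at (1, 0).

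The algebra assumes balanced data with one value per cell; the percentages also rest on the assumed variance ratios. The document therefore does not establish that the primary test has lost nearly all its power or that it gives false positives. It does establish that the named random-effects structure is a poor match to the design and is worth correcting before analysis.

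**What to change.** In Outcome measures & statistical analysis, specify random effects for participant, participant x region and participant x visit, or an equivalent covariance structure for the nine values (for example unstructured or Kronecker). Use Kenward-Roger or Satterthwaite degrees of freedom. State in advance that a component estimated at zero is dropped. Apply the same specification to pennation angle, muscle thickness, cross-sectional area and SWS. If an analysis plan already contains these terms, it is enough to align the article's wording with it.

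The cost is one line of text and two more variance parameters, with possible boundary estimates in a sample of this size. No extra participants or measurements are needed. Fixing the structure before the data are seen also spares the primary p-value from dispute over a later choice.
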